Social adversity precipitates and exacerbates clusters of mental and physical diseases and conditions (**Figure 1**). For example, socioeconomic adversity (such as having low income, being unemployed or living in a deprived area) and traumatic events (such as adverse childhood experiences, being a victim of physically violent crime or sexual assault) are linked to compounded mental and physical conditions via systemic inflammation and behavioural pathways (10, 11). The situation can be further compounded by barriers to accessing healthcare (12). For instance, people with severe mental illness may experience under-recognition and under-treatment of physical conditions such as cardiovascular disease (12–14). In turn, these clustering mental and physical conditions reinforce each other through bidirectional interactions, that are also shaped by the social and contextual factors, leading to multiplicated mortality and morbidity burdens (8).

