#### Design and study population

UK Biobank database comprises prospective biomedical data from 502,412 participants living across the UK and aged between 40 and 69 years at the time of recruitment (2006 to 2010). It benefits from data linkages to other health related records: primary care data, hospital admission data and cancer and death registries.

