#### Syndemic outcomes

The syndemic outcomes are premature mortality and all-cause hospitalisation. Mortality data are obtained from the death register based on death certificates held within the NHS Digital (England and Wales) and the NHS Central Register (Scotland) between 01/01/2011 and 30/09/2021. All-cause hospitalisation data are obtained from the Hospital Episode Statistics data - Admitted Patient Care (England), Scottish Morbidity Records – General / Acute Inpatient and Day Case Admissions (Scotland), and Patient Episode Database (Wales) between 01/01/2011 and 28/02/2018.

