#### Syndemic constructs

Syndemic constructs include social adversity (socioeconomic adversity and traumatic events) and mental, physical and oral multimorbidity.

Socioeconomic adversity will be measured by socioeconomic position (SEP) indicators at individual, household and neighbourhood (area) levels: education, employment, income and deprivation. Education is measured at an individual level and will be categorised into high (college/vocational training or above) and low (A levels, AS levels, or equivalent; O levels, GCSEs, or equivalent; CSEs or equivalent; NVQ, HND, HNC, or equivalent; other professional qualifications; and “none of the above”). Employment status is measured at an individual level and will be grouped into: employed (including those in paid employment or self-employed, or doing unpaid or voluntary work) and unemployed (including being retired, full or part time students, unemployed, looking after home and/or family, or unable to work because of sickness or disability). Income is measured by the annual total household income before taxes are deducted. It will be categorised into 0 (>£100,000), 1 (£52,000-£100,000), 3 (£31,000-£51,999), 4 (£18,000-£30,999), and 5 (<£18,000). Area deprivation is measured by Townsend deprivation index quintiles. The two quintiles with the highest area deprivation scores will be scored 1 (indicating high levels of area deprivation), and the rest of quintiles will be scored 0 (indicating low levels of area deprivation).

Traumatic events will include felt hated by family member as a child, did not feel loved as a child, physically abused by family as a child, sexually molested as a child, no one to take to doctor when needed as a child, victim of physically violent crime, victim of sexual assault, witnessed sudden violent death, belittlement by partner or ex-partner as an adult, physical violence by partner or ex-partner as an adult, sexual interference by partner or ex-partner without consent as an adult, and been involved in combat or exposed to war-zone.

Mental multimorbidity will include mood disorders and severe mental illness (ICD-10 codes: F20-F29; F31; F33-34).

Physical multimorbidity will be measured using Ronaldson et al. approach that comprises a total of 36 long term physical health conditions (**Supplementary Table 1**) (22).

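### UK BioBank codes retirees as unemployed in a cohort aged 40 to 69, so the employment indicator of adversity is strongly contaminated by age and changes meaning across the planned age strata

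*Protocol article*

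**What the plan says.** The UK BioBank section on syndemic constructs measures socioeconomic adversity by "indicators at individual, household and neighbourhood (area) levels: education, employment, income and deprivation". Employment has two levels. The favourable one is "employed (including those in paid employment or self-employed, or doing unpaid or voluntary work". The adverse one is "unemployed (including being retired, full or part time students, unemployed, looking after home and/or family", and it also takes in people too ill or disabled to work.

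The design section describes "502,412 participants living across the UK and aged between 40 and 69 years at the time of recruitment (2006 to 2010". Death and hospital admission are the outcomes: "The syndemic outcomes are premature mortality and all-cause hospitalisation".

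The Statistical analysis section controls for age, sex and ethnicity in the outcome model, uses factor analyses to select and check indicators, and answers the secondary question by stratifying on age, sex and ethnicity. It gives no separate level for retirees and no rule that makes the employment item comparable across age strata.

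**The concern.** Being out of work and being retired are different social positions. The Introduction illustrates adversity with "socioeconomic adversity (such as having low income, being unemployed or living in a deprived area". Retirement is not among the examples, and it can follow from wealth, from hardship or simply from age. At 45 the coded level will mostly describe people without work for other reasons. At 65 it will mostly describe retirees.

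The planned age strata are therefore compared on a construct in which one of four indicators changes meaning. If the path from adversity to death or admission, or its interaction with multimorbidity, differs by age, part of that difference could come from what the item records. This is a stated coding rule, not a detail left open for a fuller plan to supply.

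**Working it through.** The article gives no figure on this point to reproduce: no retirement rate and no association between employment and age. The calculation below is a sensitivity analysis.

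**From the article:** the coding rule and the age range of 40 to 69.

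**Assumed, for ages 40-49 / 50-59 / 60-69:**
- Age mix w: equal thirds, or 24/33/43%.
- Retired share R: low 0.5/5/35%, mid 1/12/60%, high 2/20/75%.
- Share of non-retired people not in work, o: 6%, 10% or 18%.

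This makes 2 × 3 × 3 = 18 scenarios.

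**Formulas, for each age band b:**
- Share coded unemployed: U_b = R_b + o(1 − R_b).
- Overall share coded unemployed: p = Σ w_b U_b.
- Retirees among those coded unemployed: R_b / U_b within a band, Σ w_b R_b / p overall.
- Share of the item's variance explained by age band: η² = Σ w_b (U_b − p)² / [p(1 − p)].

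**Central scenario (equal thirds, mid R, o = 10%):**
- U = 0.01 + 0.10 × 0.99 = 0.109; 0.12 + 0.10 × 0.88 = 0.208; 0.60 + 0.10 × 0.40 = 0.640.
- p = (0.109 + 0.208 + 0.640)/3 = 0.319.
- Retirees overall: [(0.01 + 0.12 + 0.60)/3]/0.319 = 76%. By band: 0.01/0.109 = 9%, 0.12/0.208 = 58%, 0.60/0.640 = 94%.
- η² = 0.0532/(0.319 × 0.681) = 0.245.

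**Extremes for the overall retiree share:**
- Lowest (equal thirds, low R, o = 18%): U = 0.184, 0.221, 0.467; retirees 0.405/0.872 = 46%.
- Highest (24/33/43%, high R, o = 6%): p = 0.430; retirees 0.393/0.430 = 92%.

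**All 18 scenarios:**

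| Quantity | 40-49 | 50-59 | 60-69 | Overall |
|---|---|---|---|---|
| Retirees among those coded unemployed | 3-25% | 23-81% | 75-98% | 46-92% |
| Share coded unemployed | 6-20% | 11-34% | 39-80% | 19-50% |

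Retirees are the majority overall in 17 of 18 scenarios. Age band explains 8% to 37% of the item's variance. In every scenario retirees are a minority of the coded level at 40-49 and a clear majority at 60-69.

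**The case against.** **Age is controlled, and weak items can be dropped.** Both are true. Adjustment reduces confounding of the structural paths by age, and the factor analyses may remove a poor item. Neither changes what the code records. A pooled factor analysis would average a usable loading in younger people with a weaker one in older people. Dropping the item would also discard genuine unemployment.

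**One weak item of four does little harm.** This largely stands for dilution. If the other three loadings are 0.60 (assumed) and the employment loading falls from 0.60 to 0.18-0.25, the correlation of the factor score with the latent factor is √[S/(1 + S)], with S = Σ λ²/(1 − λ²). It falls only from 0.83 to about 0.80, and the three other items alone give 0.79. If loadings are estimated freely in each stratum, education, income and deprivation will carry most of the factor in older people. The article does not say whether loadings are free or held equal. No bias in a path or interaction has been calculated.

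**A reader might infer that the item mostly measures age.** The figures do not support this. Age band explains less than half of its variance in every scenario. A simulation with 20-34% retired overall gave a correlation with age of 0.41-0.55, which is 17-30% of variance when squared.

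**A reader might infer that the loading collapses at older ages.** With an assumed true loading of 0.60, that simulation gave 0.42-0.53 under 55 and 0.08-0.13 at 60 and over. It makes retirement unrelated to adversity within age bands, which the article neither states nor excludes. With a latent correlation of +0.2 between the two, the values are 0.50-0.56 and 0.24-0.29. At −0.2 they are 0.33-0.48 and about −0.08 to −0.02. A gap between age groups remains each time, but its size depends on the assumption.

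**A reader might infer a contradiction with the Introduction, or a fault over retired volunteers.** The Introduction gives examples, not a definition. A retired volunteer does fit both levels, but precedence between statuses is a detail that a condensed article can leave to the full plan.

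**Conclusion.** The point holds as one of contamination and comparability. The rule pools retirees with people who lack work in a cohort that spans the usual retirement ages. Most people coded unemployed are likely to be retirees, and the mix reverses between the youngest and oldest bands. The percentages rest on assumed retirement rates, worklessness rates and age mixes; the reversal held in all 18 combinations.

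A difference between age strata could partly be a product of the coding. The article does not allow its size to be stated, because the other three indicators also define the factor and the treatment of loadings across strata is not given. This should be corrected before the age comparison is interpreted. It does not invalidate the primary analysis.

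**What to change.** 1. Code retired people and students as their own level, separate from those who are unemployed or unable to work. Do not score that level as adverse or non-adverse by assumption. Calling retirees non-adverse makes the mirror error for poor retirees. Setting the item to not applicable would remove it for many older participants: at an assumed 20-34% retired, about 100,000 to 171,000 of 502,412.
2. Test whether the employment loading is equal across age strata before comparing them. If it is not, free the loading or drop the item, and report which was done.
3. Keep the present coding as a sensitivity analysis.
4. Treat NHANES in the same way. Its unemployed level takes in anyone not working, and its lower occupation level includes retirees and students. Changing UK BioBank alone would weaken the harmonisation that the article aims for.

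The employment data are already held. The cost is a recoded item in two datasets, one additional test, and less information from this one of four UK BioBank indicators among older participants.

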## Introduction

The relationship between social adversity and mental, physical and oral multimorbidity is a topical yet under-researched area. A recent critical review proposed that such relationship is likely to form a syndemic (1). The review built its argument on the fact that mental disorders, physical multimorbidity and oral diseases share the same social determinants and have bidirectional relationships that are likely to have synergistic effects in terms premature mortality and excessive burden of morbidity (1–4).

Syndemics are defined as “the aggregation of two or more diseases or other health conditions in a population in which there is some level of deleterious biological or behaviour interface that exacerbates the negative health effects of any or all of the diseases involved” (5). Such adverse disease interactions can occur amongst all types of diseases infectious or non-communicable. They emerge in populations that experience social adversities such as poverty, stigmatisation, systemic discrimination and violence.

Though used interchangeably to describe the co-existence of multiple conditions in any given population, the syndemics concept goes beyond the concepts of comorbidity and multimorbidity. ‘Comorbidity’ describes the co-occurrence of additional conditions alongside a primary ‘index’ condition (6). ‘Multimorbidity’ refers to several conditions that co-exist in tandem but there is no single focus of attention on one condition over the others (7). However, ‘syndemics’ emphasise the adverse interaction between co-occurring diseases (bio-bio interaction) and underscore the role of precipitating and perpetuating adverse social, economic, environmental, political and healthcare contextual factors. These factors cluster with the myriad of diseases and shape their interaction (bio-social interaction) (8). Both types of interaction (bio-bio and bio-social) should exist to form a syndemic. The nature of these interactions should be “synergistic” rather than “additive”; meaning that the produced disease burdens are far more than the sum of disease burdens of each condition or factor alone. A few studies have operationalised the above syndemic concept correctly (8, 9).

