#### Statistical analysis

Descriptive statistics will be used to summarise participants characteristics. For NHANES and RELACHS data, survey analysis procedures will be used to account for the sample weights, stratification and clustering of the complex sampling design to ensure representative estimates.

To answer the research questions on the presence of syndemic relationships, a structural equation modelling (SEM) technique will be utilised to conceptualise syndemic constructs and model complex relationships between directly observed and indirectly observed (latent) variables. The SEM technique has gained increasing popularity in syndemic research (30, 31). To use this technique, the following steps will be undertaken:

In step one, exploratory and confirmatory factor analyses will be used to identify the clustering nature and reduce the number of indicators (observed variables) under each theoretical construct. In step two, a SEM to predict premature mortality and all-cause hospitalisation, controlling for age, sex and ethnicity, will be run. Analysis will include identifying whether the indicators chosen to measure the latent constructs are acceptable. confirmatory factor analysis will be used to provide information on how indicator items measure underlying (latent) constructs. In step three of the analysis, SEM will be used to examine the direct and indirect relationships between the constructs. The goodness of fit (GoF) of the SEM model to the data will be assessed considering the indices of Comparative Fit Index (CFI) and Tucker-Lewis Index (TLI; where values >.90 indicate a good fit), root mean square error of approximation (RMSEA), and Standardised Root Mean Square Residual (SRMR; where value <.05 indicate a good fit). In step four, the synergistic (multiplicative) interactions between different latent constructs and measured variables will be tested using two-step estimation procedures (32).

To answer the question on whether syndemic relationships vary by age, sex and ethnicity, stratified analyses by age, sex and ethnicity will be performed.

Full Information Maximum Likelihood technique will be used as a pragmatic approach for data missing estimation for SEMs. This approach produces unbiased parameter estimates and standards errors (33). For UK BioBank and RELACHS datasets, stability of exposure data over time will be checked by calculating the intraclass correlation coefficients between baseline and follow up data.

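### The UK BioBank employment indicator scores people too sick to work as socially adverse, which can bias the bio-social interaction if illness severity is incompletely measured

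*Protocol article*

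**What the plan says.** All references are to the protocol article.

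- **Indicators.** Under UK BioBank methods, Syndemic constructs, socioeconomic adversity is measured at several "levels: education, employment, income and deprivation".
- **Employment coding.** The adverse level is defined as "unemployed (including being retired, full or part time students, unemployed, looking after home and/or family, or unable to work because of sickness or disability". The part at issue is the last clause, "or unable to work because of sickness or disability". This is a stated coding rule, not a detail left open.
- **Illness.** The same section defines illness separately. Physical multimorbidity "comprises a total of 36 long term physical health conditions", and mental multimorbidity covers "mood disorders and severe mental illness (ICD-10 codes: F20-F29; F31; F33-34". The article states no severity grading for either.
- **Role of the interaction.** The Introduction says: "Both types of interaction (bio-bio and bio-social) should exist to form a syndemic". Under Statistical analysis, step four, "the synergistic (multiplicative) interactions between different latent constructs and measured variables will be tested using two-step estimation procedures".
- **Safeguards.** No separate level, exclusion or sensitivity analysis is stated for the group out of work through illness. Step one does allow factor analysis to reduce the indicators within each construct.

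**The concern.** The Introduction describes "socioeconomic adversity (such as having low income, being unemployed or living in a deprived area" as something that brings on disease. For people who stopped work because they are ill, the order is reversed: illness produced the adverse score. The Introduction itself links poor health to restricted employment, in its remarks on oral health and mental disorders.

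Among people with a listed condition, those who cannot work are likely to be the more severely ill. If the morbidity constructs record only which conditions are present, the employment item carries information on severity that they lack. The adversity-illness association is then partly built in by the coding, and an adversity-by-illness product partly reflects illness by severity of illness. At stake is the bio-social interaction, one of the two interactions on which a syndemic claim rests.

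**Working it through.** The article gives no figure on this point, so there is nothing to reproduce. The check asks whether the coding can produce an interaction when none exists, and how large.

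**From the article:** four adversity indicators; retirees, students and homemakers coded with the sick group; illness defined by diagnoses; a multiplicative interaction test; 502,412 participants in the database.

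**Assumed:** 2-8% too sick to work, 33% retired, a 7% outcome rate, and a log odds ratio of 0.5 per SD of severity among the ill.

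**Data model.** With I = illness present and V = severity,

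logit P(outcome) = a + b·I + 0.5·(I × V),

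with no effect of adversity and no adversity-by-illness term. Being too sick to work marks high V among the ill.

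**Fitted model.** logit P = α + β₁S + β₂I + β₃(S × I), where S is the adversity measure. The quantity read off is exp(β₃), which should be 1.

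**Why it departs from 1.** For the binary item, exp(β₃) = OR(S among the ill) / OR(S among the well). Nobody who is well is too sick to work, so the denominator is 1. Among the ill, the adverse level mixes ordinary non-workers with a more severely ill group, so the numerator exceeds 1.

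**Results** (illness recorded as present or absent; N = 250,000 with 8 replicates, except the 2% case, N = 100,000 with 12 replicates):

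| Adversity measure | 2% sick | 4% sick | 8% sick | Sickness left out of the item |
|---|---|---|---|---|
| Employment item alone (adverse v. not) | 1.14 | 1.21 | 1.34 | 1.01 |
| Equal-weight score of four indicators (per SD) | – | 1.04 | 1.06 | 1.00 |
| One-factor score, employment loading 0.06-0.07 | – | 1.005 | 1.007 | 1.001 |

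The rows are not on one scale: the first contrasts two levels, the second is per SD. The last column is a benchmark for the bias, not a simulation of the fix. Products of factor scores stand in for the planned two-step latent estimator.

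**When the bias vanishes.** With severity fully measured, or with severity having no effect on the outcome, the odds ratio was about 1.00 under either coding.

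**Detectability.** The equal-weight results had mean z of 2.6 (4% sick) and 3.9 (8% sick) at N = 250,000. Scaling by √(502,412/250,000) = 1.42 gives about 3.7 and 5.5. A separate run at n = 502,412, one replicate per setting, gave 1.04-1.08 with z of 3.2-6.8 for that score and 1.16-1.44 for the item. With the sick group left out, both measures gave 0.98-1.02 with |z| at most 1.2.

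**Leak through income.** When being out of work or sick also lowered income, the factor score gave 1.033-1.090 under the planned coding and 1.035-1.095 with sickness left out of the employment item. With employment dropped altogether and the smaller of the two income effects, it still gave 1.024-1.036.

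**Sensitivity to the severity model.** A harsher model let severity grow with the number of conditions and cut multimorbidity at two or more. It assumed 3.3-4.2% sick, 5% otherwise unemployed and 33% retired, with no true product. It gave 1.90-2.65 for the item and 1.16-1.24 per SD for the equal-weight score. The table is therefore an illustration, not an upper bound.

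**The case against.** **Severity may be captured.** The article refers to a supplementary table for the 36 conditions, which is not at hand. That a list of diagnoses misses severity is plausible but unverified. This stands, and makes the bias conditional.

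**Employment may carry little weight.** It is one of four indicators, and a level mixing retirees, students and the sick may load weakly or be dropped in step one. The factor score, the closest of the three measures to the planned latent model, showed almost no bias at a weak loading. This stands as a partial safeguard, but it depends on how the data fall out. Step four also covers measured variables, so a test on the employment item itself is not excluded.

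**The group is truly disadvantaged.** People unable to work are often poor, and the framework expects illness and adversity to act on each other. Some association is intended. That does not justify reading an interaction partly driven by severity as a social one.

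**Stronger readings.** A reader might infer that the coding alone creates a false interaction; the check shows that both conditions above are needed. A reader might also infer that the primary aim would be falsely answered yes. The Introduction requires a bio-bio interaction as well, so a spurious bio-social product is not enough.

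**Conclusion.** The defect is real and should be fixed before analysis, but it is conditional. A stated coding rule puts a consequence of illness into the adversity construct, and illness is the other term of the interaction under test. If unmeasured severity affects the outcome and employment keeps weight, the bio-social association and interaction can be biased.

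Under the main assumptions, the false interaction odds ratio is about 1.14-1.34 for the employment item, 1.04-1.06 for an equal-weight score and 1.00-1.01 for a weakly loaded factor. None of the assumed inputs comes from the article, so these figures show that the bias is possible, not what it will be. At the size of this database even 1.04 could reach statistical significance.

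A reader might take product odds ratios above 2 as the effect of the plan. Such values arise with employment as the only adversity measure, and the largest with retirees also left out. The plan uses four indicators and counts retirees as unemployed, so the documents do not support them.

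The concern is not confined to UK BioBank. The NHANES coding places anyone not working in the unemployed level, whatever the reason.

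**What to change.** 1. In the UK BioBank employment coding, make inability to work through sickness or disability its own category, scored neither as adverse nor as employed. Moving the group to the employed level would put the more severely ill there and push the bias the other way.
2. Do not simply leave the item blank for these people. Full information maximum likelihood would then treat it as missing, with the missingness driven by illness.
3. Repeat the adversity-by-illness interaction tests with this group excluded, and report the present coding alongside.
4. Conclude a bio-social interaction only if it persists without the group, judged on the estimate and its interval as well as the p-value.
5. State two limits. Illness-related low income may leave residual bias that recoding employment does not remove. Exclusion also takes out some of the most severely ill, so the result applies to the remaining participants.
6. Handle the NHANES not-working level in the same way where the reason for not working is recorded.

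The cost is a coding change, a repeat of the interaction models and slightly lower precision. No new data are needed for UK BioBank.

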#### Syndemic constructs

Syndemic constructs include social adversity (socioeconomic adversity) and mental, physical and oral multimorbidity. No data is available in NHANES on traumatic events.

Socioeconomic adversity will be measured by SEP indicators at individual and household levels: education, employment, occupation, income and health insurance. Education is measured at an individual level and will be categorised into high (college or above) and low (high school diploma or below). Employment status is measured at an individual level and will be grouped into: employed (working at a job or business or with a job or business but not at work) and unemployed (looking for work or not working at a job or business). Occupation is measured using socioeconomic index, which is based on the employees’ earnings, education level and prestige. It will be categorised based on the median into upper and lower level and unemployment. The lower level will include retirees and students. Income is measured by family income ratio to the federal poverty line (<100%, 100%-199%, 200%-399%, >400%). Health insurance will be categorised into private health insurance (including any private health insurance, Medi-Gap or single-service plan), public health insurance only (including Medicare, Medicaid, State Children’s Healthcare Plan, military healthcare, Indian Health Service, State Sponsored Health Plan or other government programme) and no health insurance. No data is available in NHANES on area deprivation.

Mental multimorbidity will include depression (“moderately-severe” or “severe” depressive symptoms versus “moderate”, “mild” or “no” depressive symptoms; as measured by the PHQ-9) and severe mental illness (as measured by medicines prescribed in the past month for severe mental illness).

Physical multimorbidity will be measured using Ronaldson et al. approach (**Supplementary Table 1**) (28). However, not all the 36 long term physical health conditions are reported in NHANES (such as bronchiectasis, psoriasis and polycystic ovarian syndrome). Only those that are available in NHANES will be used to indicate the physical multimorbidity construct.

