#### Syndemic constructs

Syndemic constructs include social adversity (socioeconomic adversity and adverse childhood experiences; ACEs) and mental, physical and oral multimorbidity.

Socioeconomic adversity will be measured by SEP indicators at individual, household and neighbourhood (area) levels: free school meals, car/van ownership, home ownership, parental (household) employment status and household overcrowding. Household employment status will be measured using the “dominance approach”, assigning the household the employment status of the parent/carer with the higher status.

ACEs will be measured by experiences of repeated bullying in school (“sometimes”, “about once a week” or “several times a week” versus “never bullied”, “I have not been bullied in school this term” or “once or twice”), lack of parent/carer involvement; experiences of parents often arguing or fighting; being looked after; continuing family money problems; close family dying; and home suffering damp, mould, vibration, noise from neighbours, cold, road traffic noise or dust.

Mental multimorbidity will include depression and having mental health problems. The former is measured by the Short Moods and Feelings Questionnaire (where a sore of ≥ 8 is indicative of depression). The latter is measured by the Strength and Difficulties Questionnaire (where a score of ≥ 17.5 is indicative of having mental health problems) (29).

Physical multimorbidity will be measured by having chronic illness (asthma, eczema, epilepsy, diabetes, hearing problems, eyesight problems, hay fever, chronic fatigue syndrome/ME or other chronic illness).

Oral multimorbidity will include the number of decayed teeth (as a continuous and categorical variable) and presence of toothache.

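### UK BioBank: collapsing Townsend quintiles to 0/1 discards about 38% of the continuous score's information (25% of the quintile score's) for no stated reason

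*Protocol article*

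**What the plan says.** The relevant text is in the Syndemic constructs sections of the protocol article and in Statistical analysis.

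- **UK BioBank, area deprivation.** "Area deprivation is measured by Townsend deprivation index quintiles", followed by "The two quintiles with the highest area deprivation scores will be scored 1"; the remaining three quintiles are scored 0. Deprivation is one of four socioeconomic indicators, with education, employment and income. Income keeps five ordered categories.
- **UK BioBank, mental construct.** Diagnoses, not a symptom score: "Mental multimorbidity will include mood disorders and severe mental illness (ICD-10 codes: F20-F29; F31; F33-34".
- **NHANES.** Depression is a two-level variable, with moderately severe or severe symptoms set against everything milder: "depressive symptoms; as measured by the PHQ-9". Also: "No data is available in NHANES on area deprivation".
- **RELACHS.** "Short Moods and Feelings Questionnaire (where a sore of ≥ 8 is indicative of depression", and a Strengths and Difficulties score of 17.5 or more "is indicative of having mental health problems". Both indicate the same mental construct.
- **Statistical analysis.** Factor analysis and SEM come first. In step four, "interactions between different latent constructs and measured variables will be tested using two-step estimation procedures".

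The article states no reason for the Townsend cut, no share of participants above any symptom cut, and no version of these variables that keeps more than two levels. By contrast, tooth loss (NHANES) and decayed teeth (NHANES and RELACHS) are to be used in both continuous and categorical form.

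**The concern.** The Townsend index is a graded measure with no natural threshold between the third and fourth quintiles. Reducing it to two levels treats everyone in the lower three quintiles as alike, and everyone in the upper two as alike. The detail is already in the data, and the chosen method can use it.

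What is at stake is the quality of the socioeconomic adversity construct in the largest dataset. A coarser indicator carries less information about the construct, so the construct's paths to mortality and hospitalisation are estimated less precisely. The same holds for any step-four interaction that involves the construct or the deprivation variable itself. The primary aim rests on those interactions.

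**Working it through.** The article gives no figure on this point, so there is none to reproduce. The loss can be calculated directly.

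**1. Townsend 0/1 against the continuous score.** Inputs: the share above the cut is p = 0.40 (two of five quintiles, if quintiles are formed in the sample); normality is assumed. The information kept is the squared correlation between the score and its cut version:

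kept = φ(c)² / [p(1 − p)], where c is the cut point and φ the normal density.

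With p = 0.40, φ(c) = 0.386 and p(1 − p) = 0.24, so kept = 0.386² / 0.24 = 0.622. **Lost: 37.8%.**

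Sensitivity to the assumptions:
- If the quintiles are not formed in the sample, p may differ from 0.40. The loss is 36.3% at p = 0.50, 42.4% at 0.30 and 46.1% at 0.25.
- If the score is right-skewed (gamma and exponential shapes), the loss at p = 0.40 is 38.9% to 48.4%.

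**2. Townsend 0/1 against the quintile score 1-5.** No distributional assumption is needed beyond equal quintiles.
- Variance of the quintile score: 2. Variance of the 0/1 variable: 0.4 × 0.6 = 0.24.
- Covariance: (4 + 5)/5 − 3 × 0.4 = 1.8 − 1.2 = 0.6.
- r² = 0.6² / (2 × 0.24) = 0.36 / 0.48 = 0.75. **Lost: 25%.**

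Under normality the five-level score itself has r² = 0.888 with the continuous score. Keeping the quintiles therefore loses about 11%, against 38% for the 0/1 version.

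**3. What reaches the latent construct.** In a one-factor model, an indicator with standardised loading λ contributes λ²/(1 − λ²) to the information about the factor. Treated as a plain 0/1 variable, Townsend's λ² becomes 0.622λ². The terms for education, employment and income do not change. Only one of four terms shrinks, so the construct loses proportionally less than 38%. If the 0/1 item is modelled through a threshold, the loading is not attenuated in this way, but it is still estimated from coarser data. The article names no estimator or link, which may be left to a fuller plan.

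**4. The symptom-score cuts.** The same formula applies, but the documents do not give p. Assuming normality:

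| Share above cut | Kept | Lost |
|---|---|---|
| 20% | 0.490 | 51.0% |
| 10% | 0.342 | 65.8% |
| 5% | 0.224 | 77.6% |
| 3% | 0.159 | 84.1% |

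The skewed shapes above give smaller losses: about 35-37% at 20% above the cut and 49-60% at 5%.

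**5. Does cutting create a false interaction here?** Simulations with no true interaction, at N = 502,412:
- Two normal predictors correlated 0.3, both cut (40% and 10% above), logit slopes of 0.4 per SD, about 6-7% events: 82% rejection at the two-sided 5% level. The false interaction is negative.
- Same slopes, both cut at 40%: 6-7% rejection. Correlation 0: 5%.
- Townsend cut at 40% with a genuine yes/no diagnosis (prevalence 3-20%, correlation up to 0.5): interaction odds ratio 0.99-1.03, |z| at most 0.4.

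The third case is the one that matches Townsend paired with the UK BioBank mental construct.

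**The case against.** **The cuts never meet.** A reader might infer that cutting deprivation and the symptom scores would produce a significant false interaction at UK BioBank size. The documents do not support that. Townsend is used only in UK BioBank, where the mental construct is diagnosis codes. The PHQ-9 is used only in NHANES, which has no area deprivation. The two questionnaires are used only in RELACHS and belong to one construct. The artefact needs two correlated continua that are both cut, and for Townsend with a yes/no diagnosis it is negligible. This objection stands in full. A conditional risk remains if the cut Townsend variable is multiplied by another cut continuum, such as obesity defined as BMI of 30 or more, but the article does not specify such a product.

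**The symptom cuts define the construct.** RELACHS presents its thresholds as indicating depression or mental health problems, and UK BioBank uses diagnoses, with which the NHANES variables are meant to be harmonised. Replacing case status by symptom severity changes what the construct means. This stands: total scores should not replace the cuts in the main analysis.

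**The loss on one indicator is not the loss on the construct, and the plan does not dichotomise everything.** Both are true and limit the size of the point. Neither supplies a reason for the Townsend cut, which marks no diagnosis and serves no harmonisation, since NHANES lacks the variable. That income keeps five levels in the same construct makes the collapse harder to explain.

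**Conclusion.** The point holds as a modest matter of efficiency, confined to Townsend in UK BioBank. The 0/1 coding discards about 38% of the information in the continuous score (assuming normality and 40% above the cut) and 25% of that in the quintile score (assuming equal quintiles). The socioeconomic construct as a whole loses less than this; how much less depends on loadings and an estimator that the article does not give.

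For the symptom scores, no single figure can be stated. Under normality the loss is about 51% to 84% for 20% down to 3% above the cut, and less if the scores are skewed. Quoting one range as the loss on every score would rest on shares that the documents do not contain. The false-interaction claim is not part of this conclusion.

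**What to change.** In UK BioBank, enter Townsend as the continuous score, or as five ordinal quintiles, in the factor analysis, the SEM and any interaction that uses deprivation as a measured variable. Keep the 0/1 version for descriptive tables. This needs no new data: it costs a sentence of text and some recoding. A skewed continuous score may need a transformation, which the ordinal option avoids.

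As a sensitivity analysis only, repeat the NHANES models with the total PHQ-9 score, and the RELACHS models with the total Short Moods and Feelings and Strengths and Difficulties scores. Report the share of participants above each cut, so that readers can judge how much detail the case definitions give up. The cost is one additional set of models in each of those two datasets.
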